### **4.3.3. Supportive and sensitivity analyses**

#### **4.3.3.1. Sensitivity to missing data assumptions**

As described in Sections 4.3.1 and 4.3.2, the primary analysis will use available TLFB28 data and imputed TLFB28 data for the 28-day periods where some TLFB7 data are available. This analysis is valid under a missing at random (MAR) assumption, conditional on variables included in the imputation and regression models [8]. Given the possibility of substantial missingness in the primary outcome, sensitivity analyses will be carried out to examine the robustness of the estimate from the main analysis to departures from its assumptions.

### **(1) sensitivity analysis assuming missing at random (MAR)**

Multiple imputation by chained equation (MICE) will be performed to produce 100 complete imputed datasets [9] [10]. Variables in the MI model will include the primary outcome at baseline and weeks 5, 9, 13 and 19, covariates from the analysis model, covariates associated with discontinuation, as well as other variables and measures in the collected data.

Each imputed dataset will be analysed using the same mixed effects regression model as used for the primary analysis. The results from the imputed datasets will be pooled to form a single inference following Rubin's rules [7].

Given that the primary analysis treats the baseline outcome as a dependent variable, a second sensitivity analysis of the imputed data will be undertaken in which the baseline outcome is included as a fixed covariate, and only the post-baseline outcomes treated as dependent variables. This will evaluate the impact of the assumption in the primary analysis that the conditional distribution of the baseline outcome is the same as that of the post-baseline outcomes, which may be questionable due to the inclusion criterion that is based on the baseline days of methamphetamine use.

### **(2) sensitivity analysis assuming missing not at random (MNAR)**

Pattern-mixture frameworks will be used to examine the robustness of the estimate from the primary analysis to deviations from the MAR assumption [11]. Specifically, controlled MI [12] will be used, in which incidental missing data (i.e., where the participant had not withdrawn from the study) will be imputed under a MAR assumption as described above, while missing data following trial withdrawal will be imputed under MNAR using both delta-based and reference-based methods.

Under the delta-based method [13], a fixed amount ( $\delta$ ) will be added to imputed outcomes to reflect the assumption that withdrawn participants would tend to have higher methamphetamine use than those remaining on-study. The effect of different plausible choices of  $\delta$  will be assessed, both as a constant applied to all missing time points, and as a post-withdrawal slope [14].

Under the reference-based method [11], outcomes for all withdrawn participants will be imputed using observed data from the placebo group, reflecting the assumption that their outcomes will be similar to those participants not receiving active treatment ( "jump to reference" imputation [11]).

Each of these imputed datasets will be analysed using the two methods described in the previous section.

Other MNAR approaches including the selection method [11] and shared parameter method through joint

modelling [15] may also be explored.

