## **4. STATISTICAL METHODS**

### **4.1. GENERAL CONSIDERATIONS**

#### **4.1.1. Analysis principles**

Summaries of continuous variables will be presented as means and standard deviations, or as medians and interquartile ranges, as appropriate. Categorical variables will be presented as frequencies and percentages.

For comparisons between the two randomised groups, the estimand of interest is the expected difference in outcomes between the prescribed course of LDX and usual care, among participants who receive at least one dose. This corresponds to a modified intention-to-treat (ITT) approach to the analyses, whereby all randomised participants who received at least one dose of the prescribed medication are included according to their allocated arm. That is, withdrawal prior to receiving the first dose will be handled using a principal stratum strategy, on-study death will be handled using a hypothetical strategy, and all other intercurrent events will be handled using a treatment policy strategy.

For each outcome variable, statistical significance will be assessed at the 0.05 level using a two-sided test. In addition to treatment effect estimates and p-values, 95% confidence intervals will be reported to describe uncertainty about the effect of treatment.

No adjustment for multiple testing is planned, as the primary comparison is at a single predefined time point (week 13). However, all results will be reported and interpreted by considering both the strength of the evidence and the consistency of effects across endpoints.

All analyses will be performed using SAS version 9.3 or later, and R 4.0 or later.

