#### **4.3.2. Supplementing missing TLFB28 data with available TLFB7 data**

The number of days of MA use in the past 28 days at baseline and weeks 5, 9, 13 and 19 was collected

during the study period using the 28-day timeline follow back (TLFB28) approach. At weekly visits during the study period up until week 13, the number of days of MA use in the past 7 days was also collected using the 7-day timeline follow back (TLFB7) approach.

The primary outcome measure will be based on the data collected using the TLFB28 approach. As described in Section 4.1.3, the primary analysis method (mixed effects regression) allows for missing outcome data and is valid under a missing at random (MAR) assumption. However, it is possible that there will be some 28-day periods for which the full TLFB28 outcome is missing but some TLFB7 data, covering part of that period, are available. As such, this Section describes how the available TLFB7 data will be used to supplement the missing TLFB28 data.

If at least one TLFB7 measure is available but the full 28-day outcome is not calculable and otherwise not available for a given 28-day period (i.e., the remaining TLFB7 measures are missing, along with the TLFB28 measure), multiple imputation will be employed to produce imputed 28-day outcomes based on the observed data. Specifically, imputed values for the missing TLFB7 measures will be produced using predictive mean matching based on the observed TLFB7 and TLFB28 measures, and the missing TLFB28 measures will passively imputed [6] by adding together the observed and imputed TLFB7 measures for the given 28-day period. Where a TLFB28 measure is missing and no TLFB7 measures are available for the corresponding 28-day period, the primary outcome will be left as missing.

The primary analysis method (mixed effects regression) will be applied to the imputed datasets, and the results combined according to Rubin's rules [7]. This approach allows us to use the collected 7-day measures to inform the analysis of the 28-day outcomes where they would otherwise be missing, and appropriately account for the uncertainty in doing so.

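### MNAR imputation starts only at trial withdrawal, so missing outcomes after stopping medication without withdrawing stay under MAR in every committed scenario

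*SAP*

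**What the plan says.** SAP section 4.3.3.1, part (2), divides missing outcomes by a single criterion. On one side, "incidental missing data (i.e., where the participant had not withdrawn from the study) will be imputed under a MAR assumption". On the other, "missing data following trial withdrawal will be imputed under MNAR using both delta-based and reference-based methods". The delta method rests on the assumption that "withdrawn participants would tend to have higher methamphetamine use than those remaining on-study", with delta applied "both as a constant applied to all missing time points, and as a post-withdrawal slope"; no numerical values are given. For the reference-based method, "outcomes for all withdrawn participants will be imputed using observed data from the placebo group", on the reasoning that these people's outcomes would resemble those of people without active drug. Selection and joint models are mentioned only as possibilities.

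Three other places bear on this:

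- Section 4.1.1: apart from withdrawal before the first dose and on-study death, "all other intercurrent events will be handled using a treatment policy strategy". For someone who stops medication, the outcome wanted is therefore their use after stopping.
- Section 4.3.3.4 treats stopping treatment as an event of its own, for the supplementary on-treatment estimand.
- Section 4.3.2: "If at least one TLFB7 measure is available but the full 28-day outcome is not calculable", and the 28-day measure is otherwise unavailable, the missing weeks are filled by multiple imputation and summed. One observed week is enough.

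The SAP does not define withdrawal and does not say how a participant who simply stops attending is classed.

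**The concern.** The trigger does not match its own rationale. Jump-to-reference is justified by the loss of active treatment, but it is triggered by leaving the trial. Someone who stopped lisdexamfetamine (LDX), remained enrolled and has no week-13 outcome has also lost active treatment, yet no committed scenario departs from MAR for that person. Loss to follow-up falls on either side of the line, depending on a classification that the SAP does not state.

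What is at stake is the robustness claim, not the primary estimate. Section 4.3.3.1 itself expects that missingness could be substantial. If a good part of it is labelled incidental, the reference-based analysis will lie close to the primary result whether or not that result is robust.

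**Working it through.** **1. How each pattern is handled under the current text**

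- Stopped medication, still attending, outcome observed: used as observed. Not affected.
- Withdrew from the trial, outcome missing: delta and jump-to-reference.
- Stopped medication, still enrolled, outcome missing: MAR in every committed scenario.
- Lost to follow-up: MNAR if classed as withdrawn, otherwise MAR. The SAP does not say which.
- Withdrew within the 28 days before week 13 with at least one weekly report: section 4.3.2 can impute up to 21 of the 28 days under MAR. The SAP does not say whether the weeks after withdrawal are re-imputed under MNAR.

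**2. The plan's own figures**

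The SAP gives no figure for the MNAR analysis. The illustration borrows the effect and attrition from section 3.6, whose sample size reproduces. With a difference of 4.5, an SD of 9, two-sided alpha 0.05 and 80% power, the normal approximation gives 63 per group, or 126 in total (power 80.1%). Then 126 / 0.70 = 180.

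**3. Reach of jump-to-reference**

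Assumptions: an effect of 4.5 days in those observed; m = 0.30 of the LDX arm missing at week 13 (the planned attrition); f = the share of those missing who are classed as withdrawn. The SAP does not give f. Placebo participants are imputed from their own arm either way, so only the LDX mean moves. If MAR gives the other missing participants the full effect:

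estimate = 4.5 × (1 − 0.30 × f)

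| f | Estimate (days) | Shift from 4.5 |
|---|---|---|
| 1 | 3.15 | 1.35 |
| 0.75 | 3.49 | 1.01 |
| 0.5 | 3.83 | 0.68 |
| 0.25 | 4.16 | 0.34 |
| 0 | 4.50 | 0 |

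**4. Why the gap is an upper bound**

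Let e be the effect that MAR imputation gives to missing participants not classed as withdrawn, between 0 and 4.5. Then

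estimate = 4.5 × 0.70 + 0.30 × (1 − f) × e

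At f = 0.5 this is 3.15 + 0.15 × e: 3.83 if e = 4.5, 3.49 if e = 2.25, and 3.15 if e = 0. The difference from full coverage therefore lies between 0 and 0.68 days, depending on how much of the lost effect the MAR model already captures.

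**5. Delta method**

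If delta is applied in the LDX arm only, the shift is delta × 0.30 × f. For delta = 4.5 this is 1.35 days at f = 1, 0.68 at f = 0.5 and 0.34 at f = 0.25. A delta of 9 at f = 0.5 again gives 1.35. Because delta is to be varied, a wider range can make up for the narrow trigger. Jump-to-reference has no such dial.

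**The case against.** The strongest reply is that MAR imputation here is not imputation as if still on treatment. Section 4.3.3.1(1) puts covariates associated with discontinuation and other collected measures into the imputation model. Under treatment policy, outcomes observed after stopping medication stay in the data and can inform the imputed values. Explicit on-treatment imputation appears only in section 4.3.3.4, where it is intended. This stands. A reader might infer that the plan gives these people on-treatment values, but the text does not support that. It would be nearly true only if treatment status were left out of the model or few off-treatment outcomes were observed. The SAP does not name treatment status as a predictor, so the possibility remains open.

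A reader might also infer that only formal, form-recorded withdrawals count. The SAP never says so. Section 4.4 summarises retention by time to withdrawal, which fits counting silent leavers as withdrawn, and a definition may be in the protocol. For them, the fault is at most an unstated classification in this document.

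Nor does the SAP say that the section 4.3.2 imputations are fixed before the MNAR step. Section 4.3.3.1(2) exempts no part-observed window, so the order is ambiguous rather than wrong.

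Finally, replacing the trigger outright would go too far. It could send final visits missed through government restrictions (section 4.3.3.3) into MNAR. This also stands, and it argues for an added scenario rather than a replacement.

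None of this reaches the central gap: no committed MNAR scenario covers missing outcomes in people who stopped medication but stayed enrolled.

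**Conclusion.** The point holds as a cheap improvement to a sensitivity analysis. It is not an error in the primary analysis, whose estimate is unchanged. The reference-based analysis may move the estimate too little, by up to 0.68 days if half of the missing LDX participants fall outside the trigger. That size rests on a 4.5-day effect, 30% missing and an assumed split; the real split is not in the SAP, and the difference could be close to zero if the MAR model already captures the loss of effect.

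A reader might go further and conclude that the stress test is weakest exactly where missingness is most suspect. The SAP does not support that. Data after withdrawal, where it expects higher use, are the data being tested, and it gives no counts by type of missingness.

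**What to change.** In section 4.3.3.1(2):

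- Keep the existing scenario and add one in which delta and jump-to-reference apply to all missing outcomes after the earliest of permanent treatment discontinuation, withdrawal, or last contact with no later outcome data.
- Keep observed outcomes after discontinuation as they are.
- Leave missed visits with a documented unrelated cause, such as government restrictions, under MAR.
- Include time-varying treatment status in the MAR imputation model.
- State that, in a window part-observed by weekly reports, the observed weeks are kept and the weeks after the trigger are imputed under MNAR in this analysis, not carried over from the section 4.3.2 imputation.

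The cost is SAP wording and extra programming. The section 4.3.3.4 analysis already requires identifying when treatment stopped. The added result may be less favourable to LDX. The amendment table shows that a change has already been approved after unblinding; any addition made after unblinding must be labelled as such.

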#### 4.3.3.2. Sensitivity to baseline methamphetamine use cut-off

Prior to version 7.0 of the protocol, it was possible that participants would have at least 14 days of methamphetamine use in the 28 days prior to screening, but have a baseline TLFB28 outcome less than 14, due to a gap between screening and randomisation. These participants will be included in the primary analyses, but a sensitivity analysis will be undertaken excluding any participants whose baseline TLFB28 outcome is less than 14.

#### 4.3.3.3. COVID-19 pandemic related modifications

Study recruitment and data collection was occurring when the COVID-19 pandemic began to affect Australia in March 2020. The impact of the pandemic on trial processes will be described according to recommendations in the CONSERVE 2021 Statement [16], and associated parameters will be summarised, including the discontinuation and withdrawal rates, medication adherence before and during the pandemic and any changes in participant demographics. The missing data patterns before and during the pandemic will also be compared.

Pandemic-related intercurrent events (e.g., missed visits due to government restrictions) are expected to affect participants in both treatment arms equally, and so for the primary estimand, these will be handled using a treatment policy strategy, as planned for non-pandemic-related intercurrent events [17].

Additional exploratory analyses will be conducted. Defining the pandemic onset date as 20 March 2020 (when recruitment to the study was temporarily suspended), participants' "pandemic status" is classified into three categories based on the timing of randomisation: (1) reached primary endpoint at week 13 before pandemic onset; (2) randomised and not yet reached primary endpoint at pandemic onset; (3) randomised after pandemic onset. We will explore the impact of adjusting the primary analysis for pandemic status, and will also assess the evidence of a difference in the treatment effect between subgroups of participants according to their pandemic status.

#### 4.3.3.4. Supplementary analysis

In addition to the primary analysis targeting a treatment policy estimand via a modified ITT approach, we are also interested in a hypothetical "on-treatment" estimand, assessing the treatment effect if full compliance was achieved by all individuals, and a principal stratum estimand, assessing the treatment effect amongst the subset of participants who complied with the treatment regimen.

To estimate the on-treatment estimand, outcomes after stopping treatment (in either group) will be treated as missing. All such missing outcomes will be imputed using reference-based imputation [11], whereby they are assumed to follow a similar pattern as those observed in individuals who remained on treatment, according to their assigned group. Each imputed dataset will be analysed in the same way as described for the primary analysis, and the results combined using Rubin's rules [7].

To estimate the principal stratum estimand, we will undertake a "per protocol" analysis, including individuals who had at least one follow-up assessment, did not withdraw from the study for reasons unrelated to study medication, and did not have any major protocol violations. Participants will be analysed according to the treatment they actually received, ignoring any data collected after treatment withdrawal. The per protocol dataset will be analysed in the same way as described for the primary analysis.

Because of the potential for bias in the per protocol analysis due to differences between participants who would comply with each treatment [18], we may also further undertake a complier average causal effect (CACE) analysis targeting a principal stratum estimand of the treatment effect among participants who would have complied under *both* treatment arms.

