### **4.2. SUMMARY OF STUDY DATA**

#### **4.2.1. Protocol deviations**

Protocol deviations will be summarised as the number of deviations by type (randomisation of an ineligible participant, failure to comply with study treatment, and other). All protocol deviations will be listed with a description of the deviation and the corrective action taken.

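### The per-protocol set is selected by reason for withdrawal rather than by compliance, so it does not match the complier estimand it is said to estimate

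*SAP*

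**What the plan says.** SAP Section 4.3.3.4 adds two estimands to the primary one. The second is "a principal stratum estimand, assessing the treatment effect amongst the subset of participants who complied with the treatment regimen". It is to be estimated by a per-protocol analysis "including individuals who had at least one follow-up assessment, did not withdraw from the study for reasons unrelated to study medication". A third condition excludes anyone with a major protocol violation.

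The section then says that the analysis proceeds "ignoring any data collected after treatment withdrawal", and that "The per protocol dataset will be analysed in the same way as described for the primary analysis". It recognises that a per-protocol comparison can be biased because those who would comply may differ between the treatments. For that reason it adds: "we may also further undertake a complier average causal effect (CACE) analysis". The CACE analysis is aimed at people who would comply under either arm.

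Elsewhere, Section 4.1.2 defines only the full analysis set, so Section 4.3.3.4 holds the SAP's only definition of the per-protocol set. Sections 3.5.2 and 4.2.5 show that adherence is recorded through supervised doses and take-away dispenses, daily on days 1–5 and weekly after that. Section 4.2.1 groups protocol deviations as "randomisation of an ineligible participant, failure to comply with study treatment, and other", without saying which are major.

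**The concern.** The estimand is about compliance, but the explicit selection rule is about why someone left the study. These are different things, and the rule runs against the estimand in both directions. A participant who stopped because of the medication did not complete the regimen, yet passes the withdrawal condition. A participant who took every dose until moving away is removed, together with all of their on-treatment data.

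Reason for withdrawal is also a post-randomisation event that treatment can influence. If medication-related withdrawal is more common in one arm, the rule retains different kinds of people in the two arms. Section 4.3.3.1 itself treats withdrawal as plausibly related to outcome: its delta-based analysis supposes higher methamphetamine use among those who withdrew.

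At stake is the interpretation of one supplementary result. It could be reported as a complier effect when its population is neither compliers nor a principal stratum.

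**Working it through.** **1. The plan's own figures (SAP Section 3.6).** Inputs: difference 4.5 days, SD 9 days, two-sided alpha 0.05, power 80%, 1:1 allocation, attrition 30%.

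- n per arm = 2 × (1.960 + 0.842)² × 9² / 4.5² = 2 × 7.85 × 4 = 62.8, so 63 per arm and 126 in total.
- Randomised: 126 / (1 − 0.30) = 180, or 90 per arm.

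The stated figures reproduce, and this point does not touch them. They imply 0.30 × 90 = 27 lost per arm.

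**2. The rule set against the estimand.** All cases assume at least one follow-up assessment and no violation classed as major.

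| Participant | Complied with the full regimen? | In the per-protocol set as written? |
|---|---|---|
| Completes treatment | Yes | Yes |
| Withdraws because of the medication | No | Yes |
| Withdraws for an unrelated reason, adherent until then | Until departure | No |
| Stops treatment but stays in the study | No | Yes |

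The instruction to disregard data after treatment withdrawal has work to do only if the set contains people who stopped treatment. The last row follows because the clause concerns withdrawal from the study.

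A one-word slip would not resolve the mismatch. If *related* was meant, the set would keep unrelated withdrawers, who also did not complete the regimen.

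**3. Size.** The SAP does not give the share *s* of withdrawals that are medication related, so *s* is assumed. All 27 per arm are taken as withdrawals with a follow-up assessment and no major violation.

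- Kept non-completers = 27*s*
- Dropped by the clause = 27(1 − *s*)
- Per-protocol arm = 90 − 27(1 − *s*)

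| *s* | Kept | Dropped | Per-protocol arm | Kept as share of arm |
|---|---|---|---|---|
| 10% | 2.7 | 24.3 | 65.7 | 4% |
| 20% | 5.4 | 21.6 | 68.4 | 8% |
| 50% | 13.5 | 13.5 | 76.5 | 18% |
| 75% | 20.25 | 6.75 | 83.25 | 24% |

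**4. Imbalance.** If *s* were 50% on LDX and 10% on placebo (assumed), kept non-completers would be 13.5/76.5 = 18% of one arm and 2.7/65.7 = 4% of the other. This shows that the arms can be selected differently, not that they will be.

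**The case against.** The best defence is the rest of the rule: "did not withdraw from the study for reasons unrelated to study medication, and did not have any major protocol violations". Section 4.2.1 lists failure to comply with study treatment as a deviation type, so the final condition may remove some or all non-compliers. This stands as far as it goes. A reader might infer that everyone who left because of the medication certainly stays in, or that adherence plays no part in the set. The document does not support either statement. Nor does it support the opposite, because it never says which deviations are major.

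Second, people who are kept contribute only data up to stopping treatment, and the mixed model handles the remainder under MAR. That limits their influence but does not make them compliers.

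Third, the SAP itself warns of bias from differing compliers by arm and names an analysis for the common stratum. It would be wrong to say that the authors overlooked the problem. Their warning, though, concerns comparing compliers with compliers. It does not cover a set that is not defined by compliance even within one arm.

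Fourth, the counts are upper bounds. Anyone who leaves before a first follow-up assessment fails the first condition whatever the reason, and Section 4.3.3.1 separates incidental missing data from withdrawal. No effect on the treatment estimate has been shown.

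**Conclusion.** The mismatch is real. Followed as written, Section 4.3.3.4 yields a population that does not correspond to its stated estimand, which is more than missing detail. On the assumptions above, with 20–50% of withdrawals medication related, at most about 5–14 non-completers per arm are kept and about 14–22 per arm are dropped by the clause. True numbers would be smaller if some attrition is not withdrawal, occurs before a follow-up assessment, or comes with a major violation.

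Two further inferences are tempting and should be resisted. One is that the trial's main conclusion is at risk. It is not: the primary modified ITT analysis, its missing-data sensitivity analyses and the sample size do not use this set. The other is that the CACE analysis must become mandatory. The stratum named is those who would comply under both arms, and an exclusion restriction alone does not identify it. Further assumptions are needed, such as monotonicity or principal ignorability, so whether to commit to it is a matter of judgement.

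**What to change.** In Section 4.3.3.4:

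1. Replace the withdrawal-reason clause with a compliance criterion based on supervised doses and take-away dispenses. State the threshold and the period it covers, including how adherence is counted for someone who leaves early while still adherent. A threshold measured over the whole treatment course could exclude that person just as the present clause does.
2. Define a major protocol violation, and state whether failure to comply with study treatment is one.
3. Report the per-protocol result as descriptive. Observed adherence is still post-randomisation selection, so the new set would not be a principal stratum either.
4. Reserve the principal-stratum label for the CACE analysis, if it is done, and state its identifying assumptions.

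The cost is a few sentences of SAP text and derivation of a compliance variable from data already collected. The set may become smaller. The amendment table shows that the SAP was amended after unblinding, so a threshold set now cannot be presented as prespecified and must be disclosed as post hoc.
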